## Abstract

**Background:**

Bipolar disorders (BD) is a common, chronic and disabling psychiatric condition. In addition to being characterized by significant clinical heterogeneity, notable disturbances of sleep and cognitive function are frequently observed in all phases of the disease. Currently, there is no readily available biomarker in current clinical practice to help diagnose or predict the disease course. Thus, identification of biomarkers in BD is today a major challenge. In this context, the study of electrophysiological biomarkers based on electroretinogram (ERG) measurements in BD seems highly promising. The BiMAR study aims to compare electrophysiological data measured with ERG between a group of euthymic patients with BD and a group of healthy control subjects. Secondarily, we will also describe the existing potential relationship between clinical, sleep and neuropsychological phenotypes of patients and electrophysiological data.

**Methods:**

The BiMAR study is a comparative and monocentric study carried out at the Expert Center for BD in Nancy, France. In total, 70 euthymic adult patients with BD and 70 healthy control subjects will be recruited. Electrophysiological recordings with ERG and electroencephalogram (EEG) will be performed with a virtual reality headset after a standardized clinical evaluation to all participants. Then, an actigraphic monitoring of 21 consecutive days will be carried out. At the end of this period a neuropsychological evaluation will be performed during a second visit. The primary outcome will be electrophysiological measurements with ERG flash and pattern. Secondary outcomes will be EEG data, sleep settings, clinical and neuropsychological assessments. For patients only, a complementary ancillary study, carried out at the University Hospital of Nancy, will be proposed to assess the retinal structure and microvascularization using Optical Coherence Tomography. Recruitment started in January 2022 and will continue until the end of July 2023.

**Discussion:**

The BiMAR study will contribute to identifying candidate ERG electrophysiological markers for helping the diagnosis of BD and identify subgroups of patients with different clinical profiles. Eventually, this would allow earlier diagnosis and personalized therapeutic interventions.

**Clinical trial registration:**

The study is registered at Clinicaltrials.gov, NCT05161546, on 17 December 2021 (https://clinicaltrials.gov/ct2/show/NCT05161546).

## Introduction

### Background

Bipolar disorder (BD) is a chronic and common psychiatric pathology, which can be particularly disabling. The disease has a global prevalence rate of 1–4% (1), begins at an early age, i.e. predominantly between 15 and 25 years old and persists throughout the life of patients (2). BD is characterized by a recurrence of mood depressive episodes (pathological decrease in mood and energy), hypomanic or manic episodes (pathological increase in mood and energy), or even mixed episodes (simultaneous presence of depressive and manic symptoms). These thymic episodes are interspersed with phases of clinical remission, known as “euthymic” episodes. The disease is associated with a high morbidity and mortality rate and due to the significant functional impact it induces, including during euthymic periods, BD is the cause of poor quality of life and is one of the ten most disabling diseases according to the World Health Organization (3). The diagnosis of BD is mainly clinical and can be supported using scales or questionnaires. The diagnostic delay is estimated at around 10 years. This delay is clearly related to the heterogeneity of the clinical expression of the disease (4). The study of the literature shows that this delay in treatment seriously affects the prognosis, particularly on the functional level, and constitutes a major public health problem (5). In addition, there are no biomarkers, easily usable in current practice, to help the clinical decision for the diagnosis or for predicting the course or prognosis of the disease.

Sleep disturbances and sleep/wake rhythms are major in BD. These disturbances are observed during the different phases of the disease and are major symptoms of mood episodes and belong to the diagnostic criteria for depression, hypomania and mania (6). In addition, these anomalies are also found during euthymic phases (7). Indeed, patients suffering from BD would be more likely to present a more evening chronotype and a more languid and rigid circadian type than healthy subjects as well as a decrease in the efficiency of their sleep, an increase in sleep duration, an increased sleep latency and a prolongation of the duration of awakenings after the onset of sleep (7, 8). These disturbances in sleep and wake/sleep rhythms are associated, among other things, with more frequent relapses, an alteration in quality of life and cognitive disorders (9).

Additionally, neurocognitive deficits are frequently associated with BD. Most typical deteriorations found are an impairment of episodic verbal memory, executive functions, processing speed and sustained attention (10). These troubles can be present during mood episodes but also in around 30% of patients during euthymic phases (11). Cognitive deficits of patients with BD have a direct impact on their psychosocial functioning, on the risk of relapse, on treatment adherence or even on their ability to insight (12). Their early detection associated with the identification of prognostic and predictive biomarkers of the response to cognitive and functional remediation tools is essential in order to be able to offer early and appropriate treatment.

Due to its embryological origin, the retina is an integral part of the central nervous system. The retina is a complex neural tissue, consisting of several layers of retinal neurons. They have structural and functional properties similar to cerebral neurons (13). In addition, molecules involved in brain neurotransmission such as dopamine, serotonin, glutamate or GABA, are also involved in retinal neurotransmission (14). The retina is now considered as a relevant candidate for the study of neurotransmission abnormalities in neuropsychiatric pathologies (15). The function of retinal neurons can be measured using the electroretinogram (ERG). ERG is a simple, fast, inexpensive and non-invasive process which aims to measure the electrical activity of retinal neurons in response to light stimulation and provides indicators of synaptic transmission. This technique can represent an important electrophysiological measurement in biomarker research within psychiatric diseases (16). However, studies evaluating retinal function with ERG in BD are very few (15). In addition to the electrophysiological anomalies mentioned above, structural anomalies at the retinal level have been described. Indeed, several studies carried out in optical coherence tomography (OCT) have shown that subjects with BD present a thinning of the layers of retinal neurons (17). Additionally, results also seem to suggest that retinal thinning may be related to disease progression (18).

As previously described, retinal neurons and cortical neurons have similar properties. It should be noted that measurements of retinal function with ERG and measurements of cortical function with visual evoked potentials (VEP) share the same characteristics. Indeed, both can be performed using light flash stimulation and using luminous black and white reversing checkerboard (pattern stimulation) (13). In addition, they are complementary measures for the analysis of dysfunctions of the central visual pathways (19). Thus, the combined study of VEP using EEG could be relevant and complementary to ERG for a study of all visual neural pathways in neuropsychiatric pathologies.

In this context, highlighting biomarkers in BD is now a major challenge for neuroscience research. Thus, performing electrophysiological measurements provides a unique opportunity to objectively study neurophysiology and a number of electrophysiological parameters altered in BD, could constitute markers of the disease, allowing earlier diagnosis and a guide in medical management.

### Study aims and hypotheses

The aim of the BiMAR study is to analyse the differences in the electrophysiological data measured with ERG pattern (PERG) and flash (fERG) between a group of subjects with BD in euthymic phase and a group of healthy control subjects.

Secondarily, we also want to:
Compare combined electrophysiological measurements with ERG and EEG between the two groups.Identify relations between clinical, neuropsychological and circadian phenotypes in patients with BD and electrophysiological measurements measured with ERG and EEG.

Our main hypothesis is that differences exist in the ERG and EEG measurements between subjects with BD and healthy subjects. Those differences could be identified as candidate markers for BD which, if confirmed in later studies, could be used in current practice to guide the management of patients with BD.

## Methods

### Study design

The BiMAR study is an exploratory, open-label and non-randomized comparative moncentric study applied in psychiatry and neuroscience. This research included two groups of adult subjects: a group of patients with BD in the euthymic phase and a group of healthy control subjects. No blinding procedure is planned in this research.

The BiMAR study protocol was reviewed and approved by the French ethics committee (Comité de Protection des Personnes, Ile de France IV) under the reference 2021/60. The study is also registered at Clinicaltrials.gov under the number NCT05161546. All participants in this research will give their written informed consent before the start of any clinical interview, assessment or measurement.

### Setting and participants

This study will include two groups of participants. A group of euthymic patients with BD and a group of healthy control subjects. Patients eligible for the study will be recruited from the outpatient population followed at the Expert Center for BD in Nancy (France) or followed on an outpatient basis in consultation services of the Psychotherapeutic Center of Nancy. Healthy subjects eligible for the study will be recruited locally from the general population, after a call for volunteers using posters and flyers. A first telephone contact, at least 15 days before the first visit, with interested participants will allow them to present the study in more detail, to verify the main eligibility criteria and to set an appointment for the inclusion visit.

### Inclusion and exclusion criteria

Inclusion criteria for patients were as follows: (1) been diagnosed with BD according to DSM-IV diagnostic criteria using the Mini International Neuropsychiatric Interview (MINI) (20); (2) been currently euthymic for at least 3 months prior to the study, as defined by a score below 10 on the Montgomery-Asberg Depression Rating Scale (MADRS) which assesses depression (21) and by a score below 8 on the Young Mania Rating Scale (YMRS) which assesses mania (22); (3) age 18 or more. Healthy volunteers must not suffer from a personal psychiatric pathology verified with the MINI and be at least 18 years old (20).

Non-inclusion criteria for all participants (patients and healthy subjects) are suffering from psychiatric pathology or substance use disorders according to DSM-IV criteria measured with the MINI (20), excluding BD for the patient group; suffering from neurological or retinal pathology; having a shift work or a jet-lag in the last 15 days; criteria incompatible with the use of the virtual reality headset (Retinaute^®^, BioSerenity) like having an allergy to one of the components of the textile. We will also not include persons treated by sismotherapy during the past year, persons with an uncorrected visual impairment or disabling hearing impairment that does not allow neuropsychological tests to be performed. Finally, pregnant or breastfeeding women will also be excluded as well as subjects with an intellectual disability making it difficult to participate in the study or to understand and follow informations provided to them, adults legally protected, subjects already participating in another interventional trial.

### Procedure

#### Inclusion visit

See Figure 1 for a flow diagram of the BiMAR study and following sections for details of interventions and evaluations. During the inclusion visit and before any examination or act specific to the study, all participants will be informed about objectives and progress of the study and their free, informed and written consent will be obtained. Then, an interview and a clinical examination (including the measurement of height, weight and neck circumference, measurement of visual acuity) will be carried out in order to collect socio-demographic (Date of birth, gender, education level, current occupation) and clinical data (medical history, search for addictive behavior, treatment). The mood will be assessed using MADRS and YMRS (21, 22). In women of childbearing age, a urine pregnancy test will be performed to verify the absence of a current pregnancy. The clinical assessment is based on an interview of approximately 3 h for patients with BD in order to characterize the disorders. This interview will be conducted by a trained psychiatrist or clinical psychologist. The clinical evaluation of patients will be carried out as part of a follow-up visit to the Expert Center for BD in Nancy. Clinical self-questionnaires evaluating “trait” and “state” markers of the disease will also be submitted to patients. For healthy subjects, the interview will be shorter and last an average of 1 h. It will be used to verify inclusion criteria and to eliminate exclusion criteria, in particular the absence of psychiatric disorder. In a second step, all participants will perform an ERG and EEG recording, made with a virtual reality headset and 4 EEG channels (Retinaute^®^, BioSerenity). The duration of this exam is approximately 1 h. The visit will end with an evaluation of sleep of all participants by questionnaires then by the installation of an actigraph (MotionWatch8^®^, CamNtech). The duration of the initial visit will be 1 day for the group of patients and ½ day for the group of healthy control subjects.

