### Devices

#### Retinaute^®^ (BioSerenity)

The Retinaute^®^ is a portable medical device developed by BioSerenity, France, for performing an ERG. It comes in the form of a virtual reality headset, which can be used in outpatient facilities. It is non-invasive and uses skin electrodes for the collection of parameters. Electrodes will be positioned on the lower eyelid, on the temple and on the forehead, 1 cm above the eyebrows, according to the recommendations of the developer (BioSerenity). fERG allows to study the retina in a global way thanks to a light flash delivered over the entire surface of the retina. The two main analysis parameters are the a-wave and the b-wave with two main components: the amplitude measured in microvolts and the implicit time measured in milliseconds. This allows the study of photoreceptors with the a-wave and bipolar cells with the b-wave. The Retinaute^®^ also allows the realization of a PERG to precisely study the macular area of the retina. The two main parameters are the P50 and N95 waves with two main components: the amplitude measured in microvolts and the implicit time measured in milliseconds. The P50 wave allows the study of the retinal first two layers (photoreceptors and bipolar cells). The N95 wave specifically studies ganglion cells.

PERG and fERG are performed according to the standards of the International Society for Clinical Electrophysiology of Vision (ISCEV) (23, 24). For the PERG measurements, the stimulus is a black and white contrast reversible checkerboard, with 0.8° check size, 93.3% contrast level, 100 cd/m^2^ constant luminance white area, and 4 reversals per second. Dark-adapted 0.01 fERG, dark-adapted 3.0 fERG and dark-adapted oscillatory potentials, are performed after 20 min of dark adaptation. The stimulus in each case was a flash with a strength of 0.01 and 3.0 candela^*^s/m^2^, respectively. Oscillatory potentials are recorded to the 3 candela^*^s/m^2^ flash stimuli. Then, after 10 min of light adaptation with a light background set at 30 cd/m^2^, light-adapted 3.0 fERG and light-adapted 3.0 flicker fERG are recorded. The stimulus is a flash with a strength of 3.0 candela^*^s/m^2^. These signals will be supplemented with 4 EEG channels, *via* cup electrodes applied to the skull and allowing the concomitant performance of an EEG.

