Certain limitations inherent in the interventions are known and described. They will be considered in this study. Indeed, several conditions may be associated with changes in the function and/or retinal structures. We can cite certain medical comorbidities such as obesity, diabetes, OSA, the consumption of certain toxic substances including tobacco, as well as the taking of certain medications (15). However, these comorbidities are frequently associated with BD and the disease requires long-term treatment. We know that these factors can have an impact on the ERG signal or even EEG. This is the reason why we will take it into account when processing and analyzing the data. Recording in actigraphy requires all participants to remember to press the button on the watch when going and getting out of bed. It may nevertheless be compensated through the sleep diary that will correct missing data. Also note that participants with time awake during the night by staying completely still could be counted as sleep by the device and thus overestimate sleep duration. We know that performing neuropsychological tests can require a significant attentional load, especially for patients who may have residual cognitive impairment associated with BD. This will be offset by the organization of breaks during the execution of the tests.

The ancillary study will consist of carrying out an OCT examination for the group of patients. This complementary module will allow the study of retinal structural changes within a significant sample with regard to data from the literature (56). We will also carry out a study of the retinal microvasculature, for which there is no data in the literature, to our knowledge, in patients with BD.

Finally, one of the specificities and strengths of the BiMAR study is to concomitantly combine the study of several electrophysiological markers and to associate a search for a relationship with circadian, sleep and neuropsychological markers.

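### Patients reach the ERG/EEG after a much longer assessment than controls, and no masking is planned, so prior load and any judgement on the traces are tied to group on the primary outcome

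*Protocol article*

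**What the plan says.** The Inclusion visit section fixes the order of the day. Consent comes first, then interview and examination, and then the recording: "In a second step, all participants will perform an ERG and EEG recording".

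What precedes the recording depends on group. For patients, "The clinical assessment is based on an interview of approximately 3 h for patients with BD", and they also receive self-questionnaires on trait and state markers. For controls, "For healthy subjects, the interview will be shorter and last an average of 1 h". The section closes with "The duration of the initial visit will be 1 day for the group of patients and ½ day for the group of healthy control subjects".

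On masking, the Study design section says "No blinding procedure is planned in this research".

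The recording is the primary endpoint. The abstract states "The primary outcome will be electrophysiological measurements with ERG flash and pattern", and the EEG waves are secondary.

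The Retinaute section gives one technical protocol for everyone: "PERG and fERG are performed according to the standards of the International Society for Clinical Electrophysiology of Vision (ISCEV", with 20 min of dark adaptation, 10 min of light adaptation and fixed stimulus settings. In the Discussion, the factors listed as able to alter the retina begin "We can cite certain medical comorbidities such as obesity, diabetes, OSA, the consumption of certain toxic substances including tobacco" and go on to medication. Prior assessment load, time of day and knowledge of group when traces are handled are not among them.

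**The concern.** In a comparison of patients with healthy controls, whatever is done differently to the two groups before the measurement is mixed with diagnosis. Here the article itself sets such a difference: roughly two more hours of interview for patients, plus questionnaires that controls do not complete.

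The article's own rationale makes this relevant. It describes altered sleep/wake rhythm and sustained attention in euthymic bipolar disorder, and it excludes recent shift work and jet-lag. In the Discussion it accepts that neuropsychological testing can be an attentional burden for patients, and it provides breaks for those tests.

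The lack of masking opens a second route. The sample-size section allows for non-exploitable data, so some recordings will be set aside. If that decision, or the extraction of amplitudes and implicit times, involves judgement, it would be made with group known.

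What is at stake is the primary group difference. Parameters that differ between groups then go on to ROC curves with sensitivity and specificity, so a procedural difference could be carried forward as a candidate marker. A larger sample does not help, because a systematic shift does not shrink with n.

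**Working it through.** **1. The plan's own figure.** Inputs from Sample size: standardised difference 0.5, alpha 5%, power 80%. The normal approximation for two means gives 63 per group and the two-sided t-test gives 63.8, so 64. The stated 64 is reproduced, and this point changes no stated figure. Recruitment is 70 per group with 10% loss, which leaves 70 × 0.9 = 63 evaluable. The final analysis is at 4% (Statistical analysis).

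**2. What differs by group and what does not.**

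| Feature | Patients | Controls | Source |
|---|---|---|---|
| Interview before recording | about 3 h | about 1 h | Inclusion visit |
| Trait/state questionnaires | yes | no | Inclusion visit |
| Length of visit | 1 day | ½ day | Inclusion visit |
| Clock time of recording | not stated | not stated | – |
| Stimulus and adaptation | ISCEV, 20 min dark, 10 min light | same | Retinaute section |
| Masking | none planned | none planned | Study design |

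The stated difference in interview time is 3 − 1 = 2 h. A difference in clock time is possible but does not follow: a control half-day in the afternoon could fall at the same hour as the patients' recording.

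**3. What a shift would do.** The article gives no size for any procedural effect, so a shift of b SD is assumed, with no true disease effect. For n per group and two-sided alpha:

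- df = 2n − 2 and critical value c = t(1 − alpha/2; df)
- noncentrality λ = b × √(n/2)
- rejection rate = P(|T| > c), with T noncentral t(df, λ)

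With n = 63 and alpha = 0.04: df = 124, c = 2.076, √(63/2) = 5.61. An observed difference of 2.076 × √(2/63) = 0.37 SD is then significant for one parameter.

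| Assumed b | λ | Rejection rate, n = 63 | n = 70 |
|---|---|---|---|
| 0 | 0 | 4.0% | 4.0% |
| 0.1 | 0.56 | 7.2% | 7.5% |
| 0.2 | 1.12 | 17.4% | 19.0% |
| 0.3 | 1.68 | 35.0% | 38.5% |

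The rates are per parameter. The last column confirms that more participants make a fixed shift more, not less, likely to be declared significant.

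**4. Can the analysis repair it?** Adjusting for start time separates it from diagnosis only where the two groups' start times overlap. Prior load is set by group, and on the stated schedule it barely overlaps, so it cannot be adjusted away. Masked handling of traces does not depend on overlap.

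**The case against.** The strongest reply is that the conditions at the recording itself are standardised. Stimulus, dark adaptation and light adaptation are identical, and responses are averaged within each eye and then over both eyes, so only the earlier part of the visit differs. This stands as a real mitigation. It does not equalise what came before, and it does not mask anyone.

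No recording hour is given, so a reader might infer that patients are recorded at a different time of day. The document supports only that they may be.

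A reader might also infer that a person marks wave peaks and rejects traces by eye, knowing the group. No such reader is described, and extraction may be automatic. Details of that kind may sit in the full protocol, which is not shown. What can be said is conditional: if there is judgement, nothing in the stated plan keeps it masked.

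Nor does the article say that interview fatigue alters a-wave, b-wave, P50 or N95 values. The shifts in the table are assumptions. They show consequence, not likelihood.

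Lastly, the study is declared exploratory and open-label, its markers are to be confirmed later, and recruitment began in January 2022. Reordering visits midway would mix two procedures within the sample. That is a good reason not to reorder, but it is no obstacle to masked trace handling, appointment alignment or a logged start time.

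**Conclusion.** The point holds in a limited form. The article states that prior assessment load differs by group before the primary measurement and that no blinding is planned. These are features it fixes, not details left to another document. Time of day possibly differs as well, and any judgement on extraction or exploitability would be made with group known.

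The size of the bias is unknown. If a procedural shift of 0.1, 0.2 or 0.3 SD existed, the false-positive rate for a single parameter at the 4% level with 63 per group would be about 7%, 17% or 35%. This rests on an assumed shift, a two-sided t-test and 10% loss from 70. For scale, the effect the study is sized to detect is 0.5 SD.

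The stronger reading, that fatigue, clock time or reader expectation does produce the group difference, is not supported. The documents show that these routes are open, not that any of them operates. The change is still worth making because it is cheap and acts on the primary comparison.

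**What to change.** **Masking.** Replace the no-blinding sentence in Study design with a statement that participants and operators are unmasked, but that traces are exported under the existing pseudonymised code without group label, and that parameter extraction and the decision that a recording is non-exploitable are completed before group is linked. This can be applied to all stored traces, including those already recorded.

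**Timing.** For remaining participants, book control visits so that the recording falls in the same clock-time window as in patients. Log the recording start time for everyone. Report a sensitivity analysis adjusting for start time, restricted to the range where the groups overlap.

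**Limitation.** State in the Discussion that prior load differs by group, that scheduling cannot fully equalise it, and that participants already recorded cannot be corrected in this respect.

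**Cost.** A coded-export step, one extra data field and less flexible control appointments. No additional examination and no additional participants are needed.
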